### Participants and recruitment

Potential participants from the public or KKH (patients/staff) or referred from other healthcare institutes who fulfil the inclusion criteria will be invited to participate in the HELMS study. KKH houses the largest Obstetrics and Gynaecology department in Singapore, managing approximately 12 000 deliveries a year with patients made up of a wide sociodemographic spectrum. Invitation letters, emails, messages, webpages, brochures and posters will be used for advertising. Interested women can contact the study team by email or phone.

Inclusion criteria include (1) a woman who plans to conceive in the next 12 months; (2) BMI 25–40 kg/m^2^; (3) age 21–40 years; (4) Chinese, Malay, Indian ethnicity or any combination of these three ethnic groups; (5) intending to reside in Singapore for the next 4 years; (5) can access the Internet through any digital platform and (6) can provide written informed consent. Exclusion criteria include (1) currently pregnant; (2) difficulty in understanding the English language; (3) known type 1 or type 2 diabetes; (4) being on anticonvulsant medication, oral steroid, contraception or fertility medication in the past 1 month; (5) on HIV or Hepatitis B or C medication in the past 1 month. If a woman is pregnant within 1 month from the baseline visit, they will be censored from the analyses. If a woman has a pregnancy loss and wishes to rejoin the study, she will be recharacterised at the preconception baseline visit at least 1 month after a negative urine pregnancy test and will receive intervention as before.

Women who suffer from a miscarriage or termination event, experience multiple pregnancies, with fetal congenital anomalies, cannot comply with the study protocol or wish to discontinue their participation will be withdrawn from the study.

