### Outcomes and assessments

The primary outcome is the pregnancy rate in overweight and obese women trying to conceive within 1 year of baseline assessment. It is defined by a positive urine pregnancy test, followed by ultrasound confirmation of an intrauterine gestational sac after 6 weeks of amenorrhoea. If an ultrasound scan is not available or inconclusive, the diagnosis of pregnancy will be made clinically. A successful conception is one of the most important clinical outcomes, and it represents the culmination of improved metabolic and mental health, leading to optimised gametogenesis.

Coprimary outcomes include maternal metabolic health and mental health status in each phase, with 18 months postdelivery serving as the principal endpoint. Maternal metabolic health is assessed by metabolic syndrome criteria. Mental health is evaluated using the Edinburgh Postnatal Depression Scale (EPDS).^35^

Other key outcomes include:

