#### Women/mothers

Reproductive health as assessed by fecundability, pregnancy loss and live birth rates, and sexual function based on Female Sexual Function Index-19.^36^Pregnancy outcomes include pain, obstetric and delivery complications.Health behaviours assessed by dietary practice (6P tool,^30^ 4-day food diary, Food Frequency Questionnaire,^37^ Three Factor Eating Questionnaire,^38^ alcohol and supplement intake), smoking exposure, physical activity and sedentary behaviours (International Physical Activity Questionnaire,^39 40^ Sedentary Behaviour Questionnaire,^41^ accelerometer), and sleep (Pittsburgh Sleep Quality Index,^42^ digital tracker).Metabolic profile, including weight status, body fat distribution, blood pressure, lipid and glycaemic measures.Gut microbiome profile assessed by stool sample.Nutrient status based on diet, blood and breast milk composition (breast milk will be collected at five time points through the first year postdelivery).Ocular health as assessed by retinal vessel calibre characteristics.

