#### Offspring

Anthropometry and growth assessed by antenatal serial ultrasound scans, infant weight, length and head circumference.Neonatal complications such as hypoglycaemia and admission to neonatal care facilities; infant health and well-being, and skin biopsy for a subset of infants with eczema.Infant feeding assessed by breastfeeding behaviours, time of weaning, nutrition milestone, dietary intake and eating behaviours.

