### Planned analyses

Continuous variables will be presented as means and SD, or medians and 25th–75th centiles, as appropriate. Categorical variables will be presented as numbers and percentages. The pregnancy rate will be determined by the number of women who became pregnant (defined as stated previously) divided by the total number of women who completed the 1-year follow-up during the preconception phase. The time to pregnancy (TTP) will be estimated by the number of menstrual cycles required to achieve pregnancy over 1 year of follow-up. We will use the discrete-time proportional hazards model, which analyses TTP as a discrete scale based on the number of menstrual cycles, to estimate the fecundability ratio (FR) and the 95% CI,^43 44^ accounting for left truncation and right censoring. For the other two coprimary outcomes, a linear mixed effects model will be used to examine changes in means between the baseline and follow-up metabolic markers and EPDS scores, with adjustment for baseline potential confounders (including partner’s characteristics) and duration of the intervention received. In addition to the pre–post comparison of outcomes stated above, differences in pregnancy and birth outcomes will also be compared with a similar observational cohort in Singapore called Singapore PREconception Study of long-Term maternal and child Outcomes (S-PRESTO),^45^ using multiple linear or logistic regression models, adjusting for potential confounders. These confounders, such as age, ethnicity and education, will be determined from literature review, directed acyclic graph and/or observed statistically significant associations with exposures and outcomes.

We will impute missing data using multiple imputation analyses by chained equations.^46^ The number of imputations will be determined based on a percentage of missing values,^47^ and the results of total imputations will be pooled using Rubin’s rule.^48^ To determine whether the imputation of the missing data may have affected the results, we will perform sensitivity analyses on participants with a complete set of data.

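### Withdrawing women for multiple pregnancy, fetal anomaly or loss ends follow-up before outcomes the trial lists, and may bias the S-PRESTO comparison of birth outcomes unless the same restriction applies there

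*Protocol article*

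**What the plan says.** The rule is in the protocol article, Participants and recruitment. It covers "Women who suffer from a miscarriage or termination event, experience multiple pregnancies, with fetal congenital anomalies", together with women who cannot comply or who "wish to discontinue their participation will be withdrawn from the study". Removal is therefore from the study, not only from the intervention. The same section allows re-entry after a loss: "If a woman has a pregnancy loss and wishes to rejoin the study, she will be recharacterised at the preconception baseline visit".

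The outcomes are listed as follows:

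- Women/mothers: "Reproductive health as assessed by fecundability, pregnancy loss and live birth rates", and "Pregnancy outcomes include pain, obstetric and delivery complications".
- Offspring: "Neonatal complications such as hypoglycaemia and admission to neonatal care facilities".
- Outcomes and assessments: "Coprimary outcomes include maternal metabolic health and mental health status in each phase, with 18 months postdelivery serving as the principal endpoint". Mental health is measured by the EPDS.

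Under Planned analyses, "differences in pregnancy and birth outcomes will also be compared with a similar observational cohort in Singapore", namely S-PRESTO, by regression adjusted for confounders such as age, ethnicity and education. Missing data are to be multiply imputed, with a complete-data sensitivity analysis. The section does not say whether withdrawn women stay in the denominators or are imputed, or whether S-PRESTO is restricted in the same way.

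Trial design and setting describes one exit visit, at 12 months, for women who have not become pregnant.

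**The concern.** Withdrawal is triggered by events that occur after baseline and that either are listed outcomes or plausibly predict them. Two of the triggers, multiple pregnancy and fetal anomaly, are usually recognised while the pregnancy is ongoing, so the delivery and neonatal results still lie ahead. The mother could also reach the 18-month postdelivery visit, which is the principal time point for two coprimary outcomes, but the rule takes her out first.

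Complication rates would then describe only pregnancies selected on how they developed. Adjusting for age, ethnicity and education does not undo such selection. No later analysis plan can supply data that were never collected. If S-PRESTO kept such pregnancies, the two cohorts would differ in composition for a reason unrelated to the intervention.

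For mental health, the scheduled EPDS measurements stop just when a loss may have changed the score.

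**Working it through.** **1. The plan's own attrition figures (Sample size calculation).** These reproduce.

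- Recruitment: 400 / (1 - 0.20) = 500.
- Pregnancies: 400 x 0.50 = 200.
- Losses: 200 x 0.15 = 30, leaving 170 continuing.
- Dyads: 200 x (1 - 0.15 - 0.10) = 150, as stated. Taken sequentially, 200 x 0.85 x 0.90 = 153.

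There is no separate allowance for multiples or anomalies. If they fall within the 10% drop-out (20 pregnancies), they use part of it.

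**2. What is known and what is lost, by trigger.**

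| Trigger | Known at withdrawal | Lost under the rule |
|---|---|---|
| Miscarriage, termination | The loss itself | Later EPDS and metabolic data, unless she rejoins |
| Ongoing multiple pregnancy | Pregnancy confirmed | Live birth, delivery, neonatal and 18-month maternal outcomes |
| Ongoing anomaly pregnancy | Pregnancy confirmed | As for multiples |

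**3. Numbers affected.** Rates of multiples and anomalies are not in the documents. Assume 1-3% multiples and 2-3% anomalies, so 3-6% together.

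- Of 200 pregnancies: 200 x 0.03 = 6 to 200 x 0.06 = 12.
- If the rates are applied only to the 170 continuing pregnancies: about 5 to 10.
- Women leaving after any of these events: 30 + 6 = 36 to 30 + 12 = 42 of 200. The total is slightly lower if categories overlap, for example a termination for anomaly.

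**4. Effect on a complication rate compared with S-PRESTO.** Assume a risk of 10% in the remaining pregnancies, 40-50% in multiples and 20-25% with an anomaly. There is no true intervention effect, HELMS is restricted and S-PRESTO is not.

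- Lower case, S-PRESTO rate: 0.97 x 10% + 0.01 x 40% + 0.02 x 20% = 10.5%. Odds ratio = (0.10/0.90) / (0.105/0.895) = 0.1111/0.1173 = 0.95.
- Upper case, S-PRESTO rate: 0.94 x 10% + 0.03 x 50% + 0.03 x 25% = 11.65%. Odds ratio = 0.1111 / (0.1165/0.8835) = 0.1111/0.1319 = 0.84.
- Same restriction in both cohorts: 10% against 10%, odds ratio 1.0.

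A wider set of assumptions (multiples 1-4%, anomalies 1-3%, risks of 8-10%, 50-60% and 15-30% respectively) gives odds ratios of about 0.72 to 0.95. That understates the HELMS rate by about 0.5 to 2.7 percentage points.

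**5. Effect of the denominator on loss and live birth.**

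- All confirmed pregnancies kept: loss 30/200 = 15%; continuing 170/200 = 85%.
- Withdrawn losses dropped: loss 0/170 = 0%; continuing 100%.
- All kept, but live births in 6-12 withdrawn ongoing pregnancies not recorded (taking all of them to be live births): 164/200 = 82% to 158/200 = 79% instead of 85%. This error works against HELMS.

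The article does not say which of these applies.

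**The case against.** A reader might infer that pregnancy losses disappear from the results. The text does not support that: the loss is the trigger, so it is recorded, and loss rate is a named outcome. Nor is the primary pregnancy rate altered once a pregnancy is confirmed.

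A reader might also infer that the S-PRESTO comparison is definitely tilted towards HELMS. That requires S-PRESTO to have kept multiples and anomalies. The documents do not give its exclusions, the Discussion says only that the designs are similar, and the comparator set may be defined elsewhere. Nor is the direction uniform: unrecorded live births would count against HELMS (step 5).

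Nor do 36-42 of 200 pregnancies (18-21%) lose their birth outcomes. Thirty of these are losses, with no delivery or neonatal outcome left to collect; only the 6-12 bear on birth outcomes. Even the upper-case bias is modest beside sampling error. With about 160 HELMS pregnancies at 10% risk, HELMS alone contributes sqrt(1/16 + 1/144) = 0.26 to the standard error of the log odds ratio, against a shift of 0.05-0.17, in a comparison that is not primary.

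On the EPDS, a woman who rejoins is reassessed at a new baseline, and a woman whose pregnancy is lost does not reach 18 months after that delivery. The flow diagram is not shown and might include an assessment that the text omits.

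Restricting a mother-infant growth study to singleton, non-anomalous pregnancies is also defensible as an analysis choice. These points limit the size and certainty of the problem. They do not restore the outcomes of ongoing pregnancies withdrawn by rule, or the EPDS after a loss in women who do not rejoin.

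**Conclusion.** The concern holds in a limited form. As written, the rule stops data collection for ongoing multiple and anomaly pregnancies before the delivery, neonatal and 18-month maternal outcomes the protocol lists. It also leaves no scheduled EPDS after a loss unless the woman rejoins. This holds whatever S-PRESTO did.

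The number of ongoing pregnancies is small: about 6-12 of 200 if multiples and anomalies together are 3-6%, a rate the documents do not supply. Bias in the S-PRESTO comparison is possible, and for complications it would probably favour HELMS, but it is conditional. The illustrative null odds ratio is 0.84-0.95 if S-PRESTO is unrestricted and 1.0 if it is restricted alike, and the first range rests wholly on assumed risks.

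The point is worth correcting because the missing outcomes cannot be recovered later and the remedy is cheap.

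**What to change.** Amend Participants and recruitment so that these events may end study visits but do not end outcome follow-up, where consent permits. The consent form is a supplement that is not shown, so its coverage of follow-up after withdrawal must be checked first. Specifically:

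- Keep every confirmed pregnancy in the denominators for loss and live birth, and state how a woman who rejoins is counted.
- Obtain delivery and neonatal outcomes for ongoing withdrawn pregnancies from records.
- Offer the existing questionnaire set, including the EPDS, at exit after any of these events.
- Apply any restriction to singleton, non-anomalous pregnancies identically in HELMS and S-PRESTO, and report the unrestricted HELMS results alongside.

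The cost is a wording change, record abstraction for roughly 6-12 pregnancies, one questionnaire for about 36-42 women, and slightly less favourable reported complication rates. Records may be harder to obtain for women who deliver at another hospital.

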### Intervention overview

All participants will receive an intervention via a mobile health application, designed to address and improve women’s knowledge, attitude and practice in terms of preconception-pregnancy-postpartum care and health behaviours. There will be four modules, namely the HELMS Journey, the HELMS Model, the HELMS Lifestyle and the HELMS Community. The HELMS Journey will provide anticipatory guidance on examinations and measurements performed during clinic visits. The HELMS Model will deliver the 4S (Screening, Size, Supplementation, Special considerations) care plans. The HELMS Lifestyle will provide support in healthy eating, physical activity, mental wellness and sleep hygiene. Finally, the HELMS Community will provide social support and improve participation in the programme. Each of these modules contains phase-specific information developed by obstetricians, neonatologists, paediatricians, dietitians, physiotherapists, psychiatrists and psychologists.

### Intervention details

#### HELMS journey

Details of each preconception, pregnancy and postpartum visit of HELMS will be available here to provide anticipatory guidance on these visits. This will ensure that participants are aware of the study measurements, as well as the required routine examinations.

#### HELMS model

The HELMS life-course interventions, namely 4S, are developed to provide care throughout the journey from preconception to postnatal. 4S is represented by ‘Screening’, ‘Size’, ‘Supplementation’ and ‘Special considerations’.

Screening involves health and risk assessments through physical and biomarker (eg, Anti-Mullerian hormone, glucose, insulin and lipid profile) measurements, as well as emotion and sleep evaluations for mothers, and developmental assessment for children.Body Size management encompasses education on weight status awareness and mother–child health implications, both mother–child weight tracking, healthy eating and physical activity guidance.Supplementation includes multimicronutrient, vitamin D, calcium and/or DHA supplements, which are phase specific for mother, and vitamin D supplement drops for the child.Special considerations include the management of preconception sexual health and function, the management of pregnancy symptoms and postpartum recovery, and the monitoring of infant growth and feeding management.

#### HELMS lifestyle

Metabolic health support (diet and physical activity modules).

The diet module is developed based on the 6P tool, which is designed as a platform to address metabolic health based on the principles of energy input and expenditure, as well as motivation as the basis for dietary change.^30^ It is a simple, self-administered instrument based on the concept of a mental model, which can lead to self-awareness, self-evaluation and self-education, over time resulting in a positive change in eating habits and health. The 6P comprises six components as presented in table 1. Multiple modalities are incorporated that include feedback on 6P behaviour, 6P self-monitoring, 6P goal setting and 6P nudges along with the use of the 6P tool. By including these six main discrete dietary and activity components under a single ‘package’, it will provide an overview of the mental model of nutrition based on the principle of energy input and expenditure, promoting self-awareness of unhealthy lifestyle behaviours and nudging individuals into actual implementation via concrete, personalised feedback and increasing intrinsic motivation. This is based on the theoretical framework of the theory of planned behaviour, which has been widely used to predict behavioural intention and health-related behaviours.^31^

**Table 1 T1:** Components of the 6P tool

6P	Healthy mental model of nutrition	Description
P1	Portion	Amount of food intake
P2	Proportion	Caloric density of food intake
P3	Pleasure	Frequency of snacks and sugary beverages and irregular intake
P4	Period	Time of day of food intake
P5	Physicality	Physical activity and sedentary behaviour
P6	Psychology	Readiness for change

The physical activity module seeks to engage women with the importance, type and intensity of exercise during each phase. It consists of a series of appropriate, tailored exercise videos developed by physiotherapists and obstetricians with the support of scientific evidence. Wearable activity trackers will be used to provide real-time feedback on physical performance and help participants monitor their energy expenditure. Sustainability will be supported with the use of nudges (both text messages and images) delivered weekly to influence behaviour and decision-making.

##### Mental health support (Mental health and Sleep modules)

The mental health module serves as the main way to support, screen and guide women’s mental health longitudinally. Upstream screening of depressive symptoms at the preconception stage allows women at high risk to be triaged earlier for receiving targeted mental health support from KKH’s mental health team comprising a clinical coordinator, case manager and psychiatrist. Women at medium risk will be engaged more intensively, while those at low risk will continue to participate, enabling and preparing for different stages through a package of clinical care and lifestyle support, especially in the late stages of pregnancy and early stages of postpartum. The sleep module aims to support mental wellness by promoting healthy sleep practices throughout the life-course. A wearable sleep tracker will be used to provide real-time feedback on sleep performance and help participants to monitor their sleep patterns.

#### HELMS community

An online community platform is being established as part of supporting mental health among HELMS participants. This allows women to share their experiences, identify common problems among peers and generate solutions that work for them in the online chat group.

Our intervention approach will be based on the SIGN strategy (Support, Inform, Guide and Nudge) to deliver the 4S and healthy lifestyle support. Close monitoring of women’s health allows timely support provided by the healthcare staff. Setting up mobile health education helps to inform women about the importance and warning points in different stages. Educational materials in various formats, including diagrams and videos, provide guidance on phase-specific care and healthy lifestyles that focus on nutrition, physical activity, mental health and sleep hygiene. Health nudges in the form of key messages related to preconception, pregnancy and postpartum dyad care, as well as healthy lifestyles, facilitate care support and behavioural changes. The use of nudges represents a preferred architecture strategy that is widely used in public policy making, to alter people’s behaviour and influence decision making.^32^

In summary, we will apply an interactive and personalised approach to conducting the intervention, supported by real-time feedback. This involves goal setting, individual education, self-awareness, self-monitoring, motivation and outcome review process. These techniques are commonly used in behavioural interventions and can improve health outcomes.^33 34^

### Intervention adherence

Adherence to the intervention will be established throughout the study with regular logbook charts of supplement intake, sexual activity and weight, which will be reviewed at each study visit or by telephone reminders. The use of a digital tracker for activity and sleep allows off-site monitoring of wearing adherence, and research staff will take action to check for reasons for non-adherence.

### Outcomes and assessments

The primary outcome is the pregnancy rate in overweight and obese women trying to conceive within 1 year of baseline assessment. It is defined by a positive urine pregnancy test, followed by ultrasound confirmation of an intrauterine gestational sac after 6 weeks of amenorrhoea. If an ultrasound scan is not available or inconclusive, the diagnosis of pregnancy will be made clinically. A successful conception is one of the most important clinical outcomes, and it represents the culmination of improved metabolic and mental health, leading to optimised gametogenesis.

Coprimary outcomes include maternal metabolic health and mental health status in each phase, with 18 months postdelivery serving as the principal endpoint. Maternal metabolic health is assessed by metabolic syndrome criteria. Mental health is evaluated using the Edinburgh Postnatal Depression Scale (EPDS).^35^

Other key outcomes include:

